# The MAM’Out project: a randomized controlled trial to assess multiannual and seasonal cash transfers for the prevention of acute malnutrition in children under 36 months in Burkina Faso

**DOI:** 10.1186/s12889-015-2060-3

**Published:** 2015-08-08

**Keywords:** Cash transfer, Safety nets, Acute malnutrition, Wasting, Children, Burkina Faso, Research protocol

## Abstract

**Background:**

Wasting is a public health issue but evidence gaps remain concerning preventive strategies not primarily based on food products. Cash transfers, as part of safety net approach, have potential to prevent under-nutrition. However, most of the cash transfer programs implemented and scientifically evaluated do not have a clear nutritional objective, which leads to a lack of evidence regarding their nutritional benefits.

**Methods/Design:**

The MAM’Out research project aims at evaluating a seasonal and multiannual cash transfer program to prevent acute malnutrition in children under 36 months, in terms of effectiveness and cost-effectiveness in the Tapoa province (Eastern region of Burkina Faso, Africa). The program is targeted to economically vulnerable households with children less than 1 year old at the time of inclusion. Cash is distributed to mothers and the transfers are unconditional, leading to beneficiaries’ self-determination on the use of cash. The study is designed as a two-arm cluster randomized intervention trial, based on the randomization of rural villages. One group receives cash transfers via mobile phones and one is a control group. The main outcomes are the cumulative incidence of acute malnutrition and the cost-effectiveness. Child anthropometry (height, weight and MUAC) is followed, as well as indicators related to dietary diversity, food security, health center utilization, families’ expenses, women empowerment and morbidities. 24 h-food recalls are also carried out. Individual interviews and focus group discussions allow collecting qualitative data. Finally, based on a theory framework built a priori, the pathways used by the cash to have an effect on the prevention of under-nutrition will be assessed.

**Discussion:**

The design chosen will lead to a robust assessment of the effectiveness of the proposed intervention. Several challenges appeared while implementing the study and discrepancies with the research protocol, mainly due to unforeseen events, can be highlighted, such as delay in project implementation, switch to e-data collection and implementation of a supervision process.

**Trial registration:**

ClinicalTrials.gov, identifier: NCT01866124, registered May 7, 2013.

## Background

With at least 52 million wasted children in the world [1], wasting is a crucial public health issue. Although treatments for severely acute malnourished children exist and have proven their efficacy [2, 3], curative approaches remain very expensive [4] and more evidence is needed concerning strategies related to the management of moderate acute malnutrition [5]. The second Lancet Series on Maternal and Child Under-nutrition [5] and the Scaling-Up Nutrition Initiative [6] give some recommendations on selected effective approaches for the management and prevention of under-nutrition, such as breastfeeding counselling or micronutrient supplementation, but evidence gaps still remain, particularly concerning indirect interventions. The World Health Organization highlighted in 2010 the need to consider prevention strategies when implementing programs aiming at reducing acute malnutrition rates [7]. There is also evidence showing that preventive programs, such as supplementation, can be more effective to reduce childhood under-nutrition than nutrition rehabilitation [8]. Most scientific evaluations of nutrition rehabilitation are based on product distribution [9–13]. However, products are not always locally available nor affordable for the target population. Considering the paucity of data pertaining to alternative context-adapted strategies for the prevention of acute malnutrition, research studies must be developed in order to produce evidence on effective, reproducible and cost-effective approaches [14].

Cash transfers, as part of a safety net approach, are relatively new in fragile states. Only a few safety net experiences for very poor and hunger vulnerable households have been implemented to date [15]. Indeed, humanitarian agencies have longstanding experiences with one-shot cash transfer interventions in emergency situations, but multiannual cash transfer is usually not implemented in countries exposed to acute malnutrition. Reviews on cash transfer experiences show that this type of intervention has the potential to prevent undernutrition [16, 17]. However, most of the cash transfer programs implemented and scientifically evaluated do not have a clear nutritional objective, which leads to inconclusive evidence regarding their nutritional benefits [18]. Hence, the MAM’Out (Moderate Acute Malnutrition Out) research project aims at assessing a context-adapted preventive approach, which is likely to influence several underlying causes of under-nutrition and not primarily based on food supplementation: seasonal and multiannual cash transfers. Indeed, as shown in Fig. 1, cash transfers can have an effect on all underlying causes of undernutrition. They have proven to be effective in removing financial barriers to health centers and nutritious food [19–21], especially in Latin America countries. Positive effects of cash transfer programs on poverty reduction and food security [22], diet quality [23] and child health [19, 20] have also been documented. Some reports also suggest benefices on maternal mental health [24]. One can also hypothesize that benefiting from cash transfers can allow mothers to reduce their income generating activities, leading to more time for child’s care. Most of the cited evidence comes from conditional cash transfers. However, the conditional aspect of cash transfer can be associated with several disadvantages or constraints [25] and was sometimes shown not to be appropriated, especially in African countries [26]. The MAM’Out project will thus evaluate the effects of unconditional cash transfers on the prevention of undernutrition.

**Fig. 1 Fig1:**
[figure not shown]
Proposed effects of cash transfers on the prevention of child undernutrition

Furthermore, there is a lack of evidence related to the pathways by which cash transfers can improve child nutrition outcomes. In their review’s conclusion, Gentilini and Omamo [27] highlight the need for more targeted study designs that could attribute effects to specific processes. From an intended impact pathways model, Adato and al [19] already evaluated qualitative field studies in middle income countries to explain why expected nutrition and health outcomes do or do not occur: poverty, sociocultural norms and beliefs on health care practices seem to compete with cash. This research will follow the proposition made by some authors [21, 28] to use a program theory framework to analyze the way in which different components interact in order to have an effect.

## Methods/Design

### Objectives of the research

The primary objective of the MAM’Out research project is to evaluate the effectiveness and cost-effectiveness of multiannual and seasonal cash transfers (MCTs) to prevent acute malnutrition in children under 36 months in the East region of Burkina Faso.

The specific objectives of this project are: 1. To measure the contribution of MCTs to the reduction of the incidence of acute malnutrition and morbidity for the young children; 2. To evaluate the input of MCTs in the young children’s growth and development; 3. To contribute to the creation of an evidence base on efficient preventing activities for child wasting; 4. To assess the influence of MCTs on determinants of acute malnutrition, such as food security and access to health center; 5. To evaluate the cost-effectiveness of MCTs for the prevention of acute malnutrition in order to improve their sustainability.

### Study population

The target populations are inhabitants of the Eastern region of Burkina Faso, and more specifically the Tapoa province, where Gourmanche people are in the majority. This population faces the highest fertility rate in the country, with 8.6 children per woman [29]. This leads to small interpregnancy intervals that negatively impact maternal nutritional status, leading to poor birth outcome. Results of a cross-sectional survey (SMART) aiming at estimating malnutrition prevalence in the Tapoa province in April 2012 also showed a prevalence of global acute malnutrition of 17.3 % (95 %CI: 15.2 – 19.7) among children aged 6 to 59 months (2006 WHO growth references). In this context, the MAM’Out research project specifically targets households with children under 12 months at the time of inclusion.

Thirty two (32) villages, situated in the northern part of the Tapoa province and belonging to the same livelihood zone are included in the study. Villages were selected within three municipalities, based on their geographic localization and other operational criteria, such as accessibility.

To be included in the study, households had to meet two criteria: to be classified as poor or very poor according to the Household Economy Approach [30] and to have at least one child under 1 year old at the time of inclusion, independently of his/her nutritional status. All households present in the selected villages and meeting both criteria were included in the study.

### Intervention

The proposed approach is based on monthly seasonal cash transfers for 5 months, from July to November, and for two years (2013 and 2014). A monthly 10 000 FCFA is transferred to the selected households. The amount was determined during a cash assessment study implemented in collaboration with Action Contre la Faim operational team in Burkina Faso in October 2012 and with reference to other experiences of cash transfers in the Sahel area [31]. Mothers, as the primary responsible for children’s health and nutrition, are the recipient of the cash transfer. In order to avoid destabilizing the family organization or leading to a misuse of the money, the project includes a sensitization strategy for heads of household, mothers-in-law and important people in the villages on the objectives of the project and the reasons of the choice of women as cash recipient. Cash transfers are done via mobile phones, in collaboration with a private mobile phone company chosen according to ethical criteria defined by Action Contre la Faim’s procurement department. This is a quite innovative method in Burkina Faso, as the first mobile payment system was developed only in July 2012 in the country. This way of transfer was chosen for practical and security reasons: it represents much less risks for the staff and beneficiaries. Mobile phones and SIM cards are provided to mothers.

Besides, in order to reduce the risk of drop out in the control group, compensations for the time people spent for the project are offered to all participants of this group.

### Study design and randomization

The study is designed as a two-arm clustered randomized controlled trial in the Tapoa province (Eastern region of Burkina Faso), with one group benefiting from cash transfers and one being a comparison group. The unit of randomization is the village. Subjects are assigned to the study groups according to where they live. The random assignment of the interventions is done through a ceremonial gathering with officials and community members, as well as a representative of each of the concerned villages (mainly the heads of the village). Thirty-two (32) papers with a word corresponding to one group (“cash” for the intervention group and “pas cash” for the control group) are put in a bag. Each representative of the 32 villages is asked to draw blindly from the bag a paper. The village is allocated to one of the groups according to the word on the drawn paper.

### Recruitment and informed consent

A first oral agreement is sought collectively at the community level before the beginning of the study. A representative of each village involved in the study (mainly the heads of villages and their committees) is asked to give his consent for the village participation into this research, as suggested by the WHO CIOMS Guidelines [32]. Once this first acknowledgement received, a second informed consent is sought individually. Before being enrolled in the study, heads of households and mothers are explained the aim of the research, the expected duration of their participation and the measurements that will be done. According to allocated group, each participant also receives a global explanation on the sequence of the activities and procedures. Risks and benefits associated with his/her participation are also presented. Families that refuse consent are not forced into the study because of the collective agreement. As the major part of the population is illiterate, care is taken to give all these explanations orally in the local language. Written inform consent is sought individually by a local officer part of the research team before the beginning of the study. Mothers who agree to take part in the research are asked to write down their name or make a mark with their finger print. In the second case, a second research officer or the head of the village is asked to witness the process.

### Data collection

Data collection is performed quarterly for two years by trained staff under the supervision of a field study coordinator. All participants of the study are visited every three months at home and asked to answer various questions. The collected data is immediately coded. None of the paper records includes the child’s name or address. Each field staff member has a separate register in which the correspondence between the name and address of children and the unique identification number (UIN) of children is made. In addition, heads of families are given a trial card containing information about their name and address as well as their UIN. This is to ensure that records can be accessed even in case of accidental destruction of the registers. Missing data is defined as being absent during two consecutive three-monthly visits. In such case, a home visit is organized to document the reason of the absence.

### Model theory framework

A nutritional causal analysis was conducted in the Tapoa province in November-December 2012. In addition to the already available data and context analyses, this survey allowed defining more deeply the pathways by which cash transfers can have an effect on acute malnutrition according to the local context. A model theory framework was then built and was the basis for the choice of most of the indicators followed during the study.

### Outcome measures

The primary outcomes of the study are the cumulative incidence of child wasting and the incremental cost-effectiveness ratio. Secondary outcomes are the cumulative incidence of the state of stunting, mean height-for-age Z-score, mean weight-for-length Z-score, mid-upper arm circumference (MUAC), edema, as well as rates of diarrhea, acute respiratory infections and measles.

Upon inclusion, the mother is interviewed to obtain baseline information including household composition, socio-economic status, dietary habits, child’s age, breastfeeding practices and a history of child and maternal illnesses. Intermediate factors such as food security, water access, dietary diversity scores, mother-child relationship, women’s role and health center frequentation are also asked for. During the follow up, the same information collected at inclusion time is collected again at different time points. All questionnaires were translated in local language during the training session of the data collection staff, back translated in French and pretested locally. Figure 2 summarizes the quantitative data collection throughout the two years of the study. Two 24 h-food recalls are also planned as part of children nutritional assessment.

**Fig. 2 Fig2:**
[figure not shown]
Indicators and chronogram of measurement as initially forecasted in the research protocol

Qualitative data is also collected via focus group discussions and individual interviews. Systematic focus groups are organized in all villages of the intervention group. The primary aim is to allow participants to exchange experiences of usage of the cash transfer which is part of the intervention program. Simultaneously these focus groups offer a possibility to evaluate the hypothesized action theory model of cash transfers to prevent acute malnutrition. A semi-structured questionnaire is used to assess the experiences related to all possible cash pathways. All discussions are recorded on tape. Observations made during the interviews are also reported.

### Measurement instruments

The child’s weight is recorded using an electronic mother-child weighting scale (Model 876, SECA, Germany). Length is recorded to the nearest 1 mm using foldable length boards (Model 417, SECA, Germany). MUAC is recorded using a non-stretchable plastic tape (model 201, SECA, Germany). All measurements are taken in duplicate during each home visit.

Research teams also interview for disease episodes during the last week using a standardized and tested questionnaire (acute respiratory infections, diarrhea, fever, malnutrition, malaria and measles). Diarrhea is defined as “the passage of 3 or more loose or liquid stools per day” (WHO definition). The symptoms detailed by Roth [33] are used to define acute respiratory infections: “At least one lower respiratory tract sign reported by a caregiver and/or observed by study personnel (fast or difficulty breathing, chest wall indrawing) and/or abnormal findings on pulmonary auscultation (crackles/crepitation and/or bronchial breath sounds)”. Fever is defined as a temperature superior or equal to 38 °C.

### Standardization procedure

Data collectors are trained in all procedures in order to minimize the bias linked to the data collection officers. Standardization exercises for anthropometric measures and interview techniques are organized before the beginning of the study. Questionnaires are standardized and pre-tested. Animators of the focus groups are also trained by qualified people, so that all discussion groups and individual interviews are handled in the same way.

### Sample size calculation

In order to detect a decrease with 33 % in the cumulative incidence of wasting assuming a baseline incidence rate of wasting of 0.26 per child-year [9] with a Type I error of 5 %, a statistical power of 90 % and a minimum follow-up time of 24 months, assuming a coefficient of variation K of 0.25, we calculated that 16 clusters of 50 households per cluster are necessary per study arm [34]. This calculation takes into account an anticipated 25 % drop-out.

### Statistical and qualitative analyses

Descriptive analysis will compare changes in endpoints and intermediate indicators between study groups. Cumulative incidence of wasting will be analyzed using mixed-effects Poisson regression accounting for the clustered design by village. The hypothesized change in mean weight-for-height/weight-for-length z-score will be analyzed using a linear mixed model accounting for clustering by village (random intercept). The addition of a random slope (per child) to the analysis model will be tested using a restricted maximum likelihood ratio test. Models will be adjusted for important covariates related to the child wasting incidence, namely child’s sex, child’s age, baseline nutritional status and household socio-economic score, to gain precision of model estimates. In addition, if important baseline imbalances are noticed, a sensitivity analysis will be conducted adding these imbalances to the aforementioned models. To assess the influence of missing data, a sensitivity analysis will be carried using a multiple imputation strategy to account for missing data.

Cumulative incidence of stunting and morbidity will be analyzed using mixed-effects Poisson regression accounting for the clustered design. Continuous outcomes like mean length-for-age/height-for-age z-scores, mean length/height, mean weight, mean MUAC, will be analyzed using linear mixed models adjusted for child’s sex, age and baseline condition of the outcome of interest. As a sub-analysis we will analyze the intermediate endpoints, ie after the first intervention period (2013) and the second intervention period (2014).

Cost-effectiveness will be evaluated through the calculation of cost-effectiveness ratios in terms of cost per new case of acute malnutrition averted (thanks to the cash transfer), and incremental differences in costs and outcomes between intervention and control groups [35, 36]. This will allow for the evaluation of the program effect. The measurement of total cost to achieve outcomes will be done through the ABC (Activity Based Costing) approach: ingredient costs are grouped by “cost centers” based on activities and support costs are allocated to activities based on activity time allocation from staff interviews. A separate protocol was developed in order to detail all the procedures related to the calculation of the cost-effectiveness.

Qualitative analyzes will also be conducted with data from focus groups and individual meetings with women. All recorded audio will be transcribed and translated in French into a Word document. Data obtained from these discussions will be coded using NVIVO 10.0 software. The coding will be performed by pathway corresponding to the interview guide, but also using an iterative method to integrate emerging pathways (open coding). This will allow modifying and/or validating the model theory framework constructed a priori and working on the pathways taken by cash transfers in order to have an impact of the prevention of acute malnutrition. Moreover, explorative pathway analysis will be conducted to identify the most important changes in intermediate covariates responsible for the hypothesized change in the outcome (incidence of wasting). Mediation analysis/pathway analysis will finally be performed to identify in a quantitative manner the most important pathways through which the hypothesized change in primary outcomes is mediated.

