Several challenges may still arise regarding the implementation of the study. However, to stick to the nine rounds of data collection planned in the research protocol, the end of the project is forecasted for September 2015. With a design based on a cluster randomized controlled trial, this study will lead to a strong evaluation of the effects of multiannual and seasonal cash transfers for the prevention of children acute malnutrition.

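### Morbidity is to be analysed as cumulative incidence, but last-week recall at three-monthly visits supports only a 7-day prevalence or a rate per observed child-week

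*Protocol article*

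**What the plan says.** Four parts of the protocol article bear on this point.

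- **Analysis** (Statistical and qualitative analyses): "Cumulative incidence of stunting and morbidity will be analyzed using mixed-effects Poisson regression accounting for the clustered design". Stunting and morbidity share one sentence, one quantity and one model.
- **Instrument** (Measurement instruments): "Research teams also interview for disease episodes during the last week using a standardized and tested questionnaire". The conditions listed there include diarrhoea, acute respiratory infection and measles.
- **Schedule** (Data collection): "Data collection is performed quarterly for two years by trained staff", and "All participants of the study are visited every three months at home and asked to answer various questions". The Discussion refers to the plan "to stick to the nine rounds of data collection planned in the research protocol", and the sample size section assumes "a minimum follow-up time of 24 months".
- **Outcome list** (Outcome measures): the secondary outcomes end with "as well as rates of diarrhea, acute respiratory infections and measles". In that list cumulative incidence is used for wasting and stunting, not for morbidity.

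One other item touches on illness. At inclusion the mother is asked about "breastfeeding practices and a history of child and maternal illnesses", and the inclusion items are repeated later at time points the text does not specify. No recall period is given for this item. No surveillance between visits is described.

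**The concern.** Cumulative incidence over two years is the proportion of children who have had the illness at least once by the end. Estimating it requires knowing whether illness occurred at any time in the period. For stunting, quarterly anthropometry comes close, because the state persists and most new cases will still be present at the next visit. An episode of diarrhoea or acute respiratory infection can begin and end between visits and leave no trace in a last-week question. One quantity therefore does not suit both outcomes.

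The morbidity outcomes are named secondary outcomes and form part of the first specific objective. If the analysis sentence is followed literally, they would be reported under a label that the data do not support. An analyst trying to produce the named quantity could also be led to a scoring rule, such as ever ill over follow-up, whose value depends on how often a child was seen.

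**Working it through.** The article gives no figure for the coverage of morbidity recall, so there is none to reproduce.

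**Inputs from the article:** recall window 7 days; visits every three months (about 91 days); nine rounds, read here as baseline plus eight follow-up rounds; two years, about 730 days.

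**1. Share of follow-up observed** = rounds × 7 / 730.
- Eight follow-up rounds: 56/730 = 7.7% observed, 92.3% unobserved.
- All nine rounds: 63/730 = 8.6% observed, 91.4% unobserved.

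The baseline interview looks back to the week before follow-up starts, so eight is the more relevant count. The conclusion is the same on either.

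**2. Distance between the named and the observed quantity.** Assume a constant onset rate r per child-year. Cumulative incidence over T years is 1 − exp(−rT). The eight observed weeks give T = 56/365.25 = 0.153.
- r = 1: 1 − exp(−2) = 86.5% over two years, but 1 − exp(−0.153) = 14.2% with an onset in the observed weeks.
- r = 0.1: 18.1% over two years, 1.5% in the observed weeks.

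Moving from the second figure to the first requires a model for the unobserved weeks, and the article states none.

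**3. If morbidity were scored as ever ill across rounds.** Assume a 7-day prevalence of 20% in one arm and 15% in the other (ratio 0.75), constant over time, with rounds independent within a child.
- Eight rounds: 1 − 0.80^8 = 83.2% and 1 − 0.85^8 = 72.8%, ratio 0.87.
- Six rounds attended instead of eight, at 20%: 1 − 0.80^6 = 73.8% instead of 83.2%.

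The result saturates for common illness and moves with attendance. Illness that clusters within children would soften both effects.

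**4. If positive reports were summed over whole follow-up time.** Under the same assumptions the expected counts are 8 × 0.20 = 1.6 and 8 × 0.15 = 1.2 per child, ratio 0.75. Dividing by 730 days instead of the 56 observed days lowers both absolute rates by a factor of 730/56 = 13. The factor cancels from the ratio when attendance is equal in the two arms.

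**5. Onsets versus overlapping episodes.** The 92% in step 1 is a share of time, and applies to onsets. An episode that began before the window but overlaps it may also be reported. For an assumed illness of 7 to 14 days, the onset days that lead to overlap number 7 + 7 − 1 = 13 to 7 + 14 − 1 = 20 out of about 91. Then 14% to 22% of episodes are caught and 78% to 86% are missed. This confirms that the data are period prevalences, which mix incidence with duration.

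**The case against.** The strongest reply is that this is loose wording. The outcomes section already calls these measures rates. A rate per observed child-week can be estimated from last-week recall, and mixed-effects Poisson regression is a reasonable model for it. That stands, and it limits the finding to the quantity named in the analysis section. It does not remove the finding: the analysis section names a different quantity from the outcomes section, and the described instrument cannot deliver it. An analysis plan could repair this only by departing from the published sentence.

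Three stronger readings are tempting, and the article supports none of them.

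- *The comparison of arms will be attenuated.* This follows only from ever-ill scoring, which the article nowhere states. Summed reports keep the ratio of 0.75. Measured against the named quantity, the direction reverses: with r = 1 and an assumed rate ratio of 0.80, the two-year cumulative incidence ratio is (1 − exp(−1.6))/(1 − exp(−2)) = 0.92, against 0.81 in the observed weeks.
- *Rates will be understated more than tenfold, and about 92% of measles episodes missed.* The first presumes a denominator that the article does not give and that is commonly left to the analysis plan. The second holds for onsets only (step 5 of the working).
- *Morbidity is asked about for the last week and in no other way.* The repeated illness-history item might have a longer recall, notably for measles. Its recall period is not stated and the schedule figure is not shown, so this cannot be excluded. The last-week questionnaire is nevertheless the only morbidity instrument described with a recall period.

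Unequal attendance between arms is a possibility, not something the article shows. It offers compensation to control participants to limit drop-out, and plans a multiple-imputation sensitivity analysis for missing data.

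**Conclusion.** The point holds for the named quantity. Recall covers 7.7% to 8.6% of the two years, so cumulative incidence of transient illness over follow-up is not identified from the instrument described, and the analysis and outcomes sections name different quantities for the same outcomes. The coverage figures rest only on the 7-day window, the three-monthly visits and the number of rounds. The examples with 20% and 15% prevalence, with fixed onset rates and with 7- to 14-day illness rest on assumed values and only illustrate.

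A reader might infer that the morbidity data are unusable or that the Poisson model is wrong. Neither follows: a 7-day period prevalence, or a rate per observed child-week, can be compared validly between arms with essentially the planned model. The matter concerns secondary outcomes and morbidity only. Stunting and the primary outcomes are not affected. It should be corrected before the analysis, and the correction is cheap.

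**What to change.** Reconcile the sections on outcome measures, measurement instruments and statistical analysis:

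- Define each morbidity outcome as 7-day period prevalence at each follow-up round. If a rate is preferred, use the number of reports with an offset for observed child-weeks (one per attended round).
- Analyse all attended follow-up child-rounds with mixed-effects or modified Poisson regression, or a mixed model for a binary outcome. Include random intercepts for village and child and a fixed effect for round.
- Give stunting its own sentence, so that cumulative incidence no longer covers morbidity.
- State that measles will be poorly captured by last-week recall, and interpret that outcome accordingly.

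The cost is a few sentences of outcome and model wording, with no new data. Lengthening the measles recall is not worth pursuing. The article appeared in August 2015 and the project was forecast to end in September 2015, so a change would reach at most about one of the nine rounds and would mix two recall periods in one outcome.
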